### Sample size calculation

#### Primary outcome: corrected GA at discharge

A sample size of approximately 110 parent/child dyads is required to achieve a power of 95% in a single factor analysis of variance with cGA as dependent variable and implementation status of Fine + criteria as independent variable with a global significance level of 5% when comparing 11 implementation levels/time points to prove a reduction in cGA at discharge of two weeks. The expected number of at least 300 enrolled infants (very conservative estimation) will be sufficient to prove the targeted reduction in cGA and to compensate for unknown parental study compliance and unexpected drop-outs.

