**Fig. 3 Fig3:**
[figure not shown]
Process control chart

Process control charts will be used to describe, visualize, detect and understand changes in processes of care and outcomes [39]. Crude rates or medians will be plotted using 6-month periods to provide sufficient time points for process control chart analysis while maintaining more than 40 observations for subgroups [39]. For each graph, upper and lower control limits will be determined using standard statistical process-control parameters (± 3 standard deviations) using 6 months baseline data. We aimed to have 21 data points. Special-cause variation in outcomes will be defined as (significant changes that are not part of random variation) as any data point beyond the control limits, or 6 sequential points on 1 side of the mean, in either direction [38].

Second, linear trends for changes in FCC care practices, patient characteristics, and outcomes will be analyzed using F or Wald χ2 tests from linear or logistic regression models with 6 months periods used as continuous variable. Models will be adjusted using a generalized estimating equation approach (to account for clustering) with symmetric covariance structure, for the common variables known to be associated with the outcomes: e.g. gestational age in weeks (as a categorical variable), sex, demographics, multiple births, small for gestational age, outborn status, Score for Neonatal Acute Physiology version II (SNAP II) greater than 20, antenatal steroids, and change in major medical interventions. Change in major medical interventions was included because there may be future changes such as general stem cell transplantation or artificial placenta, which may have a tremendous effect on the long term outcome.

Data management and statistical analyses will be done using Microsoft^R^ EXCEL and R version 3.2.2 A 2-sided p value of less than 0.05 will be regarded as statistically significant. Data imputation will be done by study nurses and students and cross checked by the GCP qualified investigators. Source data will remain within the study site.

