##### Background

In our department in 2018–19 in VLBW infants the mean GA was 29.0 ± 2.9 weeks. The mean cGA at discharge was 38.9 ± 4.0 weeks. Five infants were discharged beyond 45 weeks of cGA due to severe clinical complications. These infants were excluded from sample size estimation. In the remaining VLBW infants the mean GA at birth was 29.2 ± 2.8 weeks and the mean cGA at discharge was 38.3 ± 2.1 wks. In the subgroup of infants of 27 to 31 + 6/7 weeks the mean GA was 29.3 ± 1.3 weeks and mean the cGA age at discharge was 37.8 ± 1.6 weeks. In a recent paper, the cGA at discharge was 34.7 weeks in 52 infants 27–31 weeks of gestation [15]. Therefore, reduction in mean cGA at discharge by two weeks (estimated effect size 0.5–1.1) is a realistic and achievable target.

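### The 110 dyads at 95% power in an 11-level ANOVA need Cohen's f of about 0.5, which an even two-week fall does not give, and the ANOVA is not the planned trend test

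*Protocol article*

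**What the plan says.** The section on sample size for the primary outcome reads "A sample size of approximately 110 parent/child dyads is required to achieve a power of 95% in a single factor analysis of variance". The dependent variable is cGA at discharge and the factor is implementation status. The test runs at a "global significance level of 5% when comparing 11 implementation levels/time points", and its aim is "to prove a reduction in cGA at discharge of two weeks". The section then expects at least 300 enrolled infants and calls that enough for the target and for drop-outs.

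The Background under that section supplies the effect size: "reduction in mean cGA at discharge by two weeks (estimated effect size 0.5–1.1) is a realistic and achievable target". For all very-low-birthweight infants of 2018–19 it reports "The mean cGA at discharge was 38.9 ± 4.0 weeks". Five infants discharged after 45 weeks were then set aside for the sample size, which lowers the SD to 2.1. A subgroup of 27 to 31+6/7 weeks has SD 1.6. The section does not say whether the effect size is a two-group difference or Cohen's f, nor how the two weeks are distributed over the 11 levels.

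The Statistical assessment section names no ANOVA. Beside process-control charts, it says that "linear trends for changes in FCC care practices, patient characteristics, and outcomes will be analyzed" with the 6-month period as a continuous variable, adjusted for covariates through generalized estimating equations. It adds: "A 2-sided p value of less than 0.05 will be regarded as statistically significant".

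**The concern.** Two things do not fit together.

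First, the lower effect size of 0.5 equals two weeks divided by the SD of 4.0. That is a standardised difference between two groups. In an ANOVA with 11 levels the effect size f is the standard deviation of the 11 level means divided by the within-level SD. For a gradual change it is much smaller than the difference between the first and last level divided by the SD. If 0.5 was read on the wrong scale, the stated power belongs to a far larger effect than the one described.

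Second, the sample size is computed for an omnibus F test, which has no direction and cannot by itself show a reduction. The analysis section tests a slope.

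At stake are a stated power and sample size that readers will take as properties of the design, and the claim that 300 infants suffice.

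**Working it through.** **Inputs.** From the sample size section: 11 levels, alpha 0.05, a target fall of 2 weeks, N = 110, power 95%, expected enrolment 300. From its Background: SD 4.0 (all infants), 2.1 (without the five late discharges), 1.6 (subgroup), effect size 0.5–1.1. The pattern of level means is not given and has to be assumed.

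**Step 1: the plan's own figure.** One-way ANOVA power comes from the noncentral F distribution with df1 = 10, df2 = N − 11 and noncentrality λ = N·f². With f = 0.5 and N = 110, λ = 110 × 0.25 = 27.5 and power is 95.6%. The smallest N is 108, or 110 when balanced at 10 per level. Exactly 95% at N = 110 needs f = 0.493. Other values do not fit: f = 0.25 needs 400 and f = 0.55 needs 91. So, for the test named, 110 means f of about 0.5.

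**Step 2: f for an even two-week fall.** Eleven equally spaced means over 2 weeks differ by 0.2 per step. Their SD is 0.2 × √((121 − 1)/12) = 0.2 × 3.162 = 0.632 weeks, so f = 0.632/SD.

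**Step 3: power with that f.** The trend column is an unadjusted two-sided slope test with N − 2 degrees of freedom and the same λ.

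| SD (weeks) | f | ANOVA, N = 110 | ANOVA, N = 300 | Trend, N = 110 | Trend, N = 300 |
|---|---|---|---|---|---|
| 4.0 | 0.158 | 14% | 39% | 38% | 78% |
| 2.1 | 0.301 | 50% | 97% | 88% | 99.9% |
| 1.6 | 0.395 | 78% | >99.9% | 98% | >99.9% |

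The protocol's upper effect size of 1.1, read as a two-group difference, gives f = 1.1 × 0.316 = 0.348 and ANOVA power of 65% at N = 110.

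The N for 95% power with an even fall (SD 4.0, 2.1, 1.6) is 985, 279 and 166 for the ANOVA, and 522, 146 and 86 for the trend test.

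**Step 4: other patterns.** With a levels at the old mean and 11 − a levels two weeks lower, f = (√(a(11 − a))/11) × 2/SD. ANOVA power at N = 110:

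- 5 and 6 levels, SD 2.1: f = 0.474, 93%. With SD 4.0: f = 0.249, 34%.
- 3 and 8 levels, effect size 1.1: f = 0.490, about 95%.
- 2 and 9 levels, SD 1.6: f = 0.482, 94%.
- Baseline alone against ten improved levels: 12%, 41% and 68% for SD 4.0, 2.1 and 1.6.

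So 95% at 110 is approached when the full gain arrives early or midway and then holds, and the SD is about 2 or less. No such two-plateau pattern comes near it with SD 4.0, since the 5 and 6 split is the most favourable one.

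**The case against.** A reader might infer that the trial's real power is 14–50%. The documents do not support that. Those figures belong to the ANOVA, at 110 dyads, with even steps and only two of the three reported SDs. The protocol does not plan to stop at 110: recruitment runs for 5.5 years and at least 300 infants are expected. It also plans a trend test, which is more powerful for a gradual fall. This part of the objection stands.

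The even fall is an assumption. Early improvement followed by a plateau is a plausible course, and with a small SD it brings the ANOVA close to the stated 95%. That also stands, but the protocol describes new practices added every six months and states no plateau.

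That a two-group 0.5 was entered as f is an inference from the matching numbers, not something the protocol says. The mismatch in the table does not depend on it.

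SD 4.0 can be challenged because the protocol sets aside the infants behind it when planning. On the other side, the eligibility criteria do not exclude infants who are later discharged after 45 weeks, late discharge cannot be known at entry, and the quoted lower effect size equals 2/4.0. SD 4.0 is therefore a fair sensitivity case. Adjustment for gestational age and other predictors could reduce the residual SD. If all 90 eligible infants per year were enrolled (5.5 × 90 = 495, an upper limit), the unadjusted trend test would have 94% power even with SD 4.0.

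Finally, a trend test with effect size 1.1 happens to have 95% power at N = 110. The protocol, however, attaches the figure to an 11-level ANOVA.

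**Conclusion.** The statement is wrong as written for the rollout and analysis that the protocol describes. An 11-level ANOVA with 110 dyads reaches 95% power only with f of about 0.5. An even two-week fall gives 0.16 to 0.40 and power of about 14%, 50% or 78%, depending on which of the protocol's SDs applies. Independently of any assumed pattern, the test that was sized is not the test that is planned.

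The trial is not shown to be underpowered overall. At 300 infants and an even fall, the planned trend test has 99.9% power with the planning SD of 2.1, so the claim of sufficiency holds there. With SD 4.0 it has 78%, and the ANOVA 39%, so the claim does not hold at the stated 95% for the population without the late-discharge exclusion.

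These figures assume equal level sizes, independent infants, no covariate adjustment and no drop-out from the 300.

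**What to change.** Replace the 110/95% ANOVA statement with the power of the linear-trend test over the 11 half-year periods at the expected 300 infants. State the effect-size metric, the assumed mean at each level and both SDs. For a total fall of two weeks in even steps this is about 99.9% with SD 2.1 and about 78% with SD 4.0, unadjusted and with independent infants. Name the trend test as the primary analysis of cGA at discharge, so that the sample size and statistical assessment sections refer to the same test.

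The change is a rewording of the sample size section and one sentence in the analysis section. It needs no extra patients and no new data. The only cost is a less favourable stated figure for the SD of 4.0.

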##### Background

In our department in 2018–19 in VLBW infants the mean GA was 29.0 ± 2.9 weeks. The mean cGA at discharge was 38.9 ± 4.0 weeks. Five infants were discharged beyond 45 weeks of cGA due to severe clinical complications. These infants were excluded from sample size estimation. In the remaining VLBW infants the mean GA at birth was 29.2 ± 2.8 weeks and the mean cGA at discharge was 38.3 ± 2.1 wks. In the subgroup of infants of 27 to 31 + 6/7 weeks the mean GA was 29.3 ± 1.3 weeks and mean the cGA age at discharge was 37.8 ± 1.6 weeks. In a recent paper, the cGA at discharge was 34.7 weeks in 52 infants 27–31 weeks of gestation [15]. Therefore, reduction in mean cGA at discharge by two weeks (estimated effect size 0.5–1.1) is a realistic and achievable target.

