#### Exclusion criteria for infants

Exclusion criteria are severe congenital anomalies (e.g. cyanotic heart disease, severe lung hypoplasia, congenital diaphragmatic hernia), decision not to provide full life support, decision for palliative care before study entry, or parents with severe psychiatric disease.

While the intervention includes all infants admitted to the neonatal unit, only those infants meeting inclusion criteria and not meeting exclusion criteria are eligible for the study.

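### The sample size section sets aside infants discharged beyond 45 weeks cGA (SD 4.0 falls to 2.1), but eligibility and analysis keep them, so the stated power does not describe the analysed infants

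*Protocol article*

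**What the plan says.** The primary outcome is cGA at discharge. The sample size section states: "A sample size of approximately 110 parent/child dyads is required to achieve a power of 95% in a single factor analysis of variance", "with a global significance level of 5% when comparing 11 implementation levels/time points to prove a reduction in cGA at discharge of two weeks". It then relies on "The expected number of at least 300 enrolled infants (very conservative estimation" and calls that number sufficient.

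The Background under that section gives 38.9 ± 4.0 weeks for all VLBW infants in 2018–19. It continues: "Five infants were discharged beyond 45 weeks of cGA due to severe clinical complications", and "These infants were excluded from sample size estimation". The remaining infants have 38.3 ± 2.1 weeks. The target is a two-week reduction in the mean, with an effect size put at 0.5 to 1.1.

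Infants enter by gestational age and/or birthweight. The exclusion list opens "Exclusion criteria are severe congenital anomalies (e.g. cyanotic heart disease, severe lung hypoplasia, congenital diaphragmatic hernia" and goes on to limited life support, palliative care and severe parental psychiatric disease. Nothing in it concerns discharge age or length of stay.

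Statistical assessment plans control charts and, second, adjusted linear or logistic regression with 6-month period as a continuous variable. It gives no cap, truncation or separate handling for very late discharge.

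**The concern.** The five infants were set aside because of their outcome value, which is unknown at entry. The trial will enrol such infants, and the linear regression will include them. A planning SD of 2.1 would therefore describe a population that is never analysed. In variance terms the gap is (4.0/2.1)² = 3.6, so a design that looks generous with one SD may be tight with the other.

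At stake is whether 300 infants are enough for the primary outcome. A mean-based trend is also sensitive to when a few very late discharges happen to fall. Clustered early or late in the 5.5 years, they could create or mask a slope.

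**Working it through.** **Inputs from the article.** Two-sided alpha 0.05; 11 levels or periods; two-week fall; SD 4.0 (all) or 2.1 (trimmed); N = 110 (stated), at least 300 (expected). The upper figure is 90 eligible per year × 5.5 years = 495, which assumes that every eligible family consents.

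**Step 1: the plan's own figure.** One-way ANOVA power comes from the noncentral F distribution with 10 and N − 11 df and noncentrality N × f². With f = 0.50 and N = 110 (ten per level), the noncentrality is 27.5 and power is 95.6%. This reproduces the stated result.

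That f equals 2/4.0 and is also the lower end of the stated effect-size range. But 2/4.0 is a standardised difference between two means (d) on the untrimmed SD. Cohen's f is the SD of the level means divided by the within-level SD. With SD 2.1, 2/2.1 = 0.95, and none of the patterns tried gives 110:

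| Pattern of the 2-week effect, SD 2.1 | f | N for 95% (equal levels) |
|---|---|---|
| Half the levels shifted | 0.474 | 121 |
| Linear fall | 0.301 | 286 |
| Baseline versus the rest | 0.274 | 341 |
| Only the two extreme levels differ | 0.203 | 605 |

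**Step 2: power with each SD, linear fall.** Eleven means falling by 0.2 weeks per step have variance 0.2² × (11² − 1)/12 = 0.40, so their SD is 0.632. Hence f = 0.632/2.1 = 0.301, or 0.632/4.0 = 0.158. The noncentrality is N × 0.40/SD²; the trend test uses it with 1 df and the ANOVA with 10 df. No covariates.

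| N | SD | Noncentrality | Trend power | ANOVA power |
|---|---|---|---|---|
| 110 | 2.1 | 10.0 | 88% | 50% |
| 110 | 4.0 | 2.75 | 38% | 14% |
| 300 | 2.1 | 27.2 | 99.9% | 97% |
| 300 | 4.0 | 7.5 | 78% | 39% |
| 495 | 4.0 | 12.4 | 94% | 65% |

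At 400 infants and SD 4.0, trend power is 88%. For 95% trend power the required N is 146 with SD 2.1 and 522 with SD 4.0.

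**Step 3: covariates.** The planned regression is adjusted, but no R² is given. Assuming 10%, 20% or 30% of variance explained, the residual SD is 4.0 × √(1 − R²) = 3.79, 3.58 or 3.35. Trend power at N = 300 is then 82%, 86% or 90%.

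**Step 4: the shape of the tail.** The 2018–19 cohort size n is not stated. Solving 38.9n = 38.3(n − 5) + 5m gives a mean for the five of m = 38.3 + 0.12n: 49.1 weeks if n = 90, 56.3 if n = 150, 58.7 if n = 170. I simulated N = 300 with a skewed tail matched to the reported SDs, over assumed cohort sizes in this range:

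- Ordinary regression: about 76–81% power if late-discharged infants share the two-week fall, about 70–75% if they do not.
- cGA capped at 45 weeks: about 97–99%.
- Rank-based trend: at least 99%.

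**The case against.** Several points on the other side stand.

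- **One scenario is not the result.** The 78% needs N = 300, which the plan itself calls a floor, and no covariates. Expected accrual and the planned adjustment both raise it.
- **No test is labelled primary.** A reader might infer that the primary trend test falls from near certainty to under 80%. The article powers an ANOVA and lists charts and trend regression, without naming one as primary. This does not rescue the plan, because the ANOVA loses more.
- **SD 2.1 is not shown to have produced 110.** A reader might infer that trimming made the sample size too small. The stated N instead matches an effect size built on 4.0. What the document shows is a conflict between its text and its number. That a d was entered as an f is the likeliest explanation, but still an inference.
- **The true SD is uncertain.** Some of the five might have met a listed exclusion, and eligibility also admits infants above 1500 g at up to 32 + 0 weeks. Neither supports trimming on the outcome.
- **The target is a mean.** Replacing the mean outright is debatable, and capping changes what is estimated.

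Two further readings are not supported. The line "Crude rates or medians will be plotted using 6-month periods" is generic, and a descriptive median chart can sit beside a mean regression without contradiction. Handling of death before discharge may be left to a fuller document that is not shown. Nor does the article say whether family-centred care can shorten these long stays; it attributes them only to severe complications.

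**Conclusion.** The point holds as a mismatch between the planning and analysed populations, together with a sample size that its own text does not explain. With the SD of all infants and a linear two-week fall, 300 infants give about 78% unadjusted trend power and about 39% for the 11-level ANOVA. The claim that 300 is sufficient at the planned 95% is therefore not supported at that N. Trend power ranges from about 70% (late-discharged infants unaffected, no covariates, N = 300) to about 94% (495 infants, unadjusted), with 82–90% at 300 under the assumed covariate range.

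Separately, 110 infants do not give 95% ANOVA power for a linear two-week fall with either SD: about 50% with 2.1 and 14% with 4.0. These figures assume equal periods, a straight-line fall and independent infants. A step change shared by half the levels would be more favourable to the ANOVA.

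**What to change.** 1. State which SD and which effect-size measure (d or f) gave 110, and reconcile this with the sentence that sets the five infants aside.
2. Restate power at the expected N, for the test that will be used, with the SD of all analysed infants: 4.0 if the outcome is uncapped. Show the assumed pattern of change over the 11 periods.
3. Keep every infant. Prespecify a robust trend analysis of cGA at discharge (rank-based, median regression, or capped at 45 + 0 weeks) next to the mean regression, and name which is primary. If a cap is chosen, quote the SD of the capped outcome.

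This is a change of wording and analysis plan on data already being collected, with no extra recruitment. The cost is a less favourable stated power. If the robust analysis is made primary, the reduction in mean cGA becomes a secondary figure.

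### The effect size of 0.5–1.1 does not follow from the two-week target and the printed SDs, and at the SD of the set said to be used, 110 infants do not reach 95% power

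*Protocol article*

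**What the plan says.** The subsection on the primary outcome, under Sample size calculation in the protocol article, states: "A sample size of approximately 110 parent/child dyads is required to achieve a power of 95% in a single factor analysis of variance". The test is at a global 5% level over 11 implementation levels or time points, and its aim is "to prove a reduction in cGA at discharge of two weeks". At least 300 enrolled infants are expected, and this number is said to be enough and also to cover poor compliance and drop-out.

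The Background part that follows gives local data from 2018–19:

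- All VLBW infants: "The mean cGA at discharge was 38.9 ± 4.0 weeks".
- Five of them went home after 45 weeks because of severe complications. Of these five it says: "These infants were excluded from sample size estimation".
- The VLBW infants who remain: "the mean cGA at discharge was 38.3 ± 2.1 wks".
- The subgroup born at 27 to 31+6/7 weeks: "mean the cGA age at discharge was 37.8 ± 1.6 weeks".

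It concludes that a "reduction in mean cGA at discharge by two weeks (estimated effect size 0.5–1.1) is a realistic and achievable target". This range is the only effect size in the section. It is not labelled as a standardised mean difference or as Cohen's f, and no value is named as the input to the 110.

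**The concern.** A target in weeks and an SD in weeks fix the standardised difference. Here the target and all three SDs stand in one paragraph, so the printed range can be checked directly, and it fails at both ends. The upper end matches none of the SDs. The lower end matches only the set that the text says was not used. The value for the set that was used is never printed.

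At stake is the stated sample size. If 110 dyads do not give 95% power for two weeks at the SD of the planning set, then the stated number, the stated power and the spare capacity implied by setting 110 against 300 all need restating. This is not a detail left to an analysis plan: it is a printed figure that disagrees with inputs printed beside it.

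**Working it through.** **Inputs, all from the sample size section.** Target 2 weeks; SDs 4.0, 2.1 and 1.6 weeks; 11 levels; alpha 5%; power 95%; N about 110; expected enrolment at least 300.

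**Step 1: standardised difference, d = 2/SD.**

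- All VLBW: 2/4.0 = 0.50.
- VLBW without the five late discharges: 2/2.1 = 0.95.
- 27 to 31+6/7 weeks: 2/1.6 = 1.25.

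An upper end of 1.1 needs SD = 2/1.1 = 1.82. Any value that rounds to 1.1 (1.05 to 1.15) needs an SD between 2/1.15 = 1.74 and 2/1.05 = 1.90. No printed SD lies there. Rounding of the SDs does not close the gap: an SD of 2.05 to 2.15 gives 0.93 to 0.98, and an SD of 1.55 to 1.65 gives 1.21 to 1.29.

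**Step 2: reproduce the stated 110.** Power of the one-way ANOVA comes from the noncentral F with 10 and N − 11 degrees of freedom and noncentrality λ = N·f².

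- f = 0.5: λ = 110 × 0.25 = 27.5, power 95.6% at N = 110. The smallest N is 108, or 110 at ten per level. This matches the stated figure.
- f = 1.1: N = 31 is enough.
- d = 1.1 converted to f: 211 with an even fall over the levels; 99 (nine per level) with the most favourable pattern of means.

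Only f = 0.5 gives the plan's number. That is an inference from matching figures, because the document names no input.

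**Step 3: f for the set said to be used.** f is the SD of the 11 level means divided by the within-level SD, here 2.1.

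- Largest possible f for a two-week range: five levels at one end and six at the other. The SD of the means is 2 × √(5 × 6)/11 = 0.996, so f = 0.996/2.1 = 0.474.
- Even fall of 0.2 weeks per level: the SD of the means is 0.2 × √10 = 0.632, so f = 0.632/2.1 = 0.301.

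**Step 4: power and required number at SD 2.1.**

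| Pattern of means | f | Power at 110 | N for 95% | N for 95%, equal levels | Power at 300 |
|---|---|---|---|---|---|
| Most favourable (5 against 6) | 0.474 | 93.1% | 118 | 121 | over 99.9% |
| Even fall | 0.301 | 49.6% | 279 | 286 | 96.6% |

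With an even fall, 300 − 279 = 21 infants remain for drop-out, or 300 − 286 = 14 if the levels are to be of equal size.

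**The case against.** The strongest case on the other side has four parts.

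- **The 1.1 does no work.** A reader might infer that the sample size was computed from 1.1 and is too small for that reason. The document does not support this. Neither f = 1.1 (31 infants) nor d = 1.1 (99 or 211, by pattern) gives 110, while f = 0.5 does. This part stands, and no consequence for the sample size should be drawn from 1.1.
- **Realism rests on a clinical comparison.** The claim that two weeks is achievable follows from 37.8 weeks locally against 34.7 weeks in a cited cohort of similar gestation, a gap of 3.1 weeks. For that subgroup d is 1.25, so 1.1 is cautious. This also stands; the point here is the arithmetic and the stated power, not whether two weeks is plausible.
- **The value 0.95 lies inside the printed range, and 1.1 may be a blend.** Pooling the SDs 2.1 and 1.6 equally gives 1.07, and averaging 0.95 and 1.25 gives 1.10. Neither step is documented, and a cohort blended with a subgroup of similar infants describes no defined population. This does not rescue the range.
- **Enrolment is enough anyway.** At SD 2.1 with an even fall, 300 infants give about 97% power. A reader might infer that the trial is underpowered, and at 300 that does not follow from these two patterns. It answers a different question from whether 110 gives 95%, which at SD 2.1 it does not under any pattern of a two-week range over equal levels. The even fall is an assumption, but the shortfall under the most favourable pattern needs no such assumption.

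**Conclusion.** The point holds. The printed range should read 0.50, 0.95 and 1.25 for the three populations. The 1.1 has no source in the text, and the 0.5 comes from a set that the text sets aside.

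For the set said to be used, 110 infants give at most about 93% power, and about 50% under an even fall, against the stated 95%. The required number is about 118 at best and about 279 with an even fall.

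These figures rest on 11 equal levels, a two-week range between the highest and lowest level mean, a common within-level SD of 2.1 and the unadjusted ANOVA that the section describes. The gap under the most favourable pattern is small. The size of the gap beyond that depends on a pattern of means that the document does not give. The match of 110 with f = 0.5 suggests, without showing it, that a standardised difference of 0.5 may have been entered as Cohen's f.

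**What to change.** In the Background part of the sample size section, replace 0.5–1.1 by three standardised mean differences, each with its population: 0.50 (all VLBW), 0.95 (VLBW without discharges beyond 45 weeks) and 1.25 (27 to 31+6/7 weeks).

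In the primary outcome subsection, state the SD, the effect measure (d or f) and the pattern of means over the 11 levels that were used for planning. Then restate either the required number or the power at 110 and at 300 for SD 2.1 (d = 0.95), and state the room left for drop-out on that basis.

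The cost is one corrected figure and a few sentences. Enrolment and conduct need not change. The spare capacity will look smaller than 110 against 300 suggests: with an even fall it is about 21 infants.
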